### Participant timeline

The timetable for data collection is presented in Table 4. Research coordinators from each enrollment site will screen potential participants for eligibility, obtain informed consent, enroll patients and their caregivers, and perform random allocation. They will then conduct EMR review and administer surveys at baseline (t_0_), 2 months (t_1_), and 6 months (t_2_).

**Table 4 Tab4:** Timetable for data collection

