### Sample size

We calculated our sample size to ensure sufficient power to detect a clinically meaningful difference in both our primary outcome (ACP) and our principal secondary outcome (QOL) between the study arms. With an alpha of 0.05 and power of 90%, we estimate a sample size of 56 participant per study arm to detect a 30 percentage point difference in ACP at 6 months, based on effect sizes from previous studies and conservatively assuming that 30% of patients in the enhanced standard care arm will have ACP [26, 36]. After accounting for a 20% attrition rate over the study period, the adjusted final sample size based on our primary outcome is 70 participants per study arm (140 participants total). The sample size calculation based on our principal secondary outcome of QOL, measured by FACIT-Pal, is based on a recent study, which found that palliative care was associated with a standardized mean difference (SMD) in QOL of 0.46 (95% CI 0.08–0.83) [28]. With an alpha of 0.05 and power of 80%, and after accounting for a 20% attrition rate, we estimate a sample size of 80 participants per study arm (160 participants total) to detect a SMD in QOL of 0.5. To ensure adequate power for both outcomes, we will plan to enroll 160 participants. We will seek to recruit a caregiver alongside each patient as a patient-caregiver dyad, but a lack of caregiver participation will not preclude a patient's enrollment. Our total potential sample size for the trial is therefore 320 participants, including 160 patients and 160 caregivers.

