### Statistical analysis plan

Intention-to-treat analysis will be used with each patient to be included in the group to which they were assigned at randomization regardless of adherence to the intervention or crossover. Descriptive statistics will be performed and presented as means with standard deviations, medians with ranges, or frequencies with proportions, overall and by study arm. To estimate the treatment effect on completion of ACP, we will use a logistic regression model with study arm as the primary predictor and enrollment site and cancer stage (AJCC stage III or IV) as the covariates. The exponentiated coefficient for the study arm will estimate the odds ratio of ACP comparing the intervention arm to the enhanced standard of care arm. Any other covariates that are differentially distributed by study arm will also be included in the model for adjustment. To estimate the treatment effect on QOL, we will use generalized mixed-effects linear regression modeling with a random intercept and robust variance estimate. We will use longitudinal generalized mixed-effects modeling methods for all other secondary outcomes. We will report the effect size, standard error, and 95% confidence interval for the estimate of the treatment effects at 6 months.

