### Protocol non-adherence and missing data

We expect missing values to be minimal due to the ability to retrieve the outcome data even for patients who pass away or withdraw from the study through chart review and caregiver-provided information. Missing data on the baseline covariates are expected to be within 5%. Mixed-effects models can account for missing data under the assumption of missing at random (MAR), where it is assumed that missing scores depend on patient covariates in the model as well as the scores at previous time points. In addition, depending on the proportion of losses to follow-up, we will employ a different strategy for sensitivity analyses. If we observe > 5% missing data at the patient-level and an assumption of MAR is plausible, we will perform multiple imputation to address partial data. Missing outcome data will be imputed, and the treatment effect will be estimated under different scenarios to enable comparison of different sensitivity analyses.

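### The QOL model names a random intercept and no other covariance structure; if dropout after early decline differs by arm, the 6-month effect can be biased, and robust variance does not correct that

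*Protocol article*

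**What the plan says.** In the Statistical analysis plan section of the Protocol article, the QOL (FACIT-Pal) model is a mixed-effects linear regression "with a random intercept and robust variance estimate". The quantity reported is the effect size with its standard error and the "95% confidence interval for the estimate of the treatment effects at 6 months". No random slope, residual correlation or unstructured covariance is mentioned. Under Participant timeline, surveys fall at baseline, 2 months and 6 months, so the gaps are 2 and 4 months.

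Under Protocol non-adherence and missing data, the article states: "Mixed-effects models can account for missing data under the assumption of missing at random (MAR". It explains the assumption as one in which "missing scores depend on patient covariates in the model as well as the scores at previous time points". Imputation is conditional and belongs to the sensitivity analyses: "If we observe > 5% missing data at the patient-level and an assumption of MAR is plausible, we will perform multiple imputation". The same section expects little missing data because outcomes can be retrieved from charts and caregivers. The Sample size section nevertheless budgets for loss: "After accounting for a 20% attrition rate over the study period".

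**The concern.** A random intercept with independent residuals gives every pair of visits the same correlation and every visit the same variance. In advanced cancer, with gaps of 2 and 4 months, one would expect the baseline-to-6-month correlation to be the lowest of the three.

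This matters because of the role the article gives the mixed model. When a patient has no 6-month score, the fitted covariance decides how the baseline and 2-month scores stand in for it. If the covariance is wrong, the implied 6-month score can be wrong for patients who left after declining. A robust (sandwich) variance leaves that estimate where it is and adjusts only its standard error.

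Missing FACIT-Pal scores are realistic here. The instrument is the participant's own rating of the past 7 days, taken by telephone, and chart review cannot supply it. Dropout could also differ by arm, since the intervention arm has weekly community health worker check-ins and the comparator has standard care plus a brochure. What is at stake is a modest shift in the effect on the principal secondary outcome, the outcome that sets the enrolment target (80 per arm, against 70 for advance care planning).

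**Working it through.** **The plan's own figure.** With a standardized difference of 0.5, 80% power and alpha 0.05 (two-sided assumed), n per arm = 2(1.960 + 0.842)² / 0.5² = 62.8, so 63, or 64 with the t distribution. Then 64 / 0.80 = 80 per arm. The stated 80 reproduces, and this point does not dispute it.

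**Why the covariance affects the estimate.** Assume unit variances and correlations (0-2, 2-6, 0-6 months) of 0.7/0.6/0.4. The correct weights for predicting the 6-month score are:
- baseline: (0.4 − 0.6 × 0.7) / (1 − 0.7²) = −0.02 / 0.51 = −0.04
- month 2: (0.6 − 0.4 × 0.7) / (1 − 0.7²) = 0.32 / 0.51 = 0.63

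Under equal correlation ρ, both weights are ρ / (1 + ρ). Taking ρ near the average, (0.7 + 0.6 + 0.4) / 3 = 0.57, gives 0.36 each. For a patient who starts a above the mean and is b from the mean at month 2, the random-intercept prediction is too high by about (0.36 + 0.04)a + (0.36 − 0.63)b = 0.40a − 0.27b. This is positive when a > 0 and b < 0, that is, after a decline. If dropout simply follows a low month-2 score, a averages 0.7b and the error is 0.28b − 0.27b, about zero. So decline-driven dropout makes an arm look too good at 6 months, and the treatment effect moves only if the two arms are affected unequally.

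**Size.** The check was a large-sample simulation with a true 6-month effect of 0.50 SD. Baseline was treated as an outcome with a common mean. Dropout after month 2 followed a logistic model in the observed change from baseline to month 2, so it is MAR. A random-intercept and an unstructured model were fitted by maximum likelihood with the same mean model.

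From the article: the visit times, 6 months as the reporting time, the 20% attrition and the effect of 0.5. Assumed: the correlations, the strength of the link between decline and dropout, how dropout differs by arm, and that all dropout falls after month 2.

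Decline drives dropout in the control arm, dropout is random in the intervention arm, 20% in each:

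| Correlations 0-2 / 2-6 / 0-6 | Random intercept | Unstructured |
|---|---|---|
| 0.7 / 0.6 / 0.4 | 0.445 | 0.495 |
| 0.7 / 0.7 / 0.5 | 0.452 | 0.501 |
| 0.6 / 0.5 / 0.3 | 0.449 | 0.496 |
| 0.6 / 0.6 / 0.6 (equal) | 0.494 | 0.494 |

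In the last row both models agree, so the covariance misfit causes the shift. If decline drives dropout in the intervention arm only, the sign reverses.

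Other dropout patterns, first three correlation sets, random-intercept estimate:
- same mechanism and rate in both arms: 0.50
- decline drives dropout in both arms, twice as strongly in control: 0.48
- same dependence on decline, 25% control against 15% intervention: 0.47-0.48
- control-only dependence, with half the dropout before month 2 at random: 0.46-0.47

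**Consequence.** With 64 completers per arm and a simple two-sample comparison, SE = √(2/64) = 0.177. Power is 81% at 0.50 and 72% at 0.45. A bias of 0.05 is 0.05 / 0.177 = 0.28 SE, so coverage of a nominal 95% interval is Φ(1.68) − Φ(−2.24), about 94%.

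**Precision of the alternative.** With 80 per arm, the unstructured model's standard error was 2-3% smaller.

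**The case against.** The strongest objection is that the article contains no error here. It is a condensed account, residual covariance for a secondary outcome is detail often left to the analysis plan, and the sentence does not exclude further structure. That stands in part: a reader might infer that the plan rules out anything beyond a random intercept, and the text does not say so. It does, however, name one structure and qualify it with nothing but a robust variance, so the point concerns a stated choice rather than an omission.

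A reader might also infer that a wrong covariance, or dropout after decline, by itself biases the treatment effect. Neither does. With the same mechanism and rate in both arms the bias cancels, and with a truly equal correlation there is none.

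The 0.05 figure rests on a stark contrast: decline matters in one arm and not at all in the other. Once decline matters in both arms, the shift is 0.02-0.03. The article applies the same tracing and the same survey payment to both arms, which argues against a large difference. Shifts of up to about 0.13 SD can be produced, but they need assumptions such as 30% against 10% dropout, or one-arm dependence with steeper decay or growing variance. Nothing in the article supports those inputs.

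Finally, the 20% attrition budget exceeds the 5% trigger for multiple imputation, and an unrestricted imputation model could reveal a covariance-driven shift. That is true, but it is a sensitivity analysis and would leave the main estimate as it is.

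**Conclusion.** The point holds as a cheap improvement to the principal secondary analysis. The structure named for QOL is restrictive for three unequally spaced visits, the article relies on that model under MAR, and a robust variance does not repair the point estimate. Two conditions must both hold for the treatment effect to be biased: a true covariance without equal correlation and variance, and dropout after early decline that differs between arms in rate or in dependence on decline.

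Under the three assumed correlation sets and about 20% dropout, the bias on a true 0.50 runs from 0 to about 0.05 SD, with its direction set by the arm affected. The correlations, the dropout mechanism and its difference by arm are all assumptions, as is treating baseline as an outcome, which the article leaves open. These results do not show that the trial's QOL estimate will be biased, that the sample size is wrong, or that the primary analysis of advance care planning is affected.

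**What to change.** In the Statistical analysis plan section, replace the random intercept in the QOL sentence with an unstructured covariance across baseline, 2 and 6 months. Keep the robust variance if wanted. State in advance that the random-intercept model is used only if the unstructured model fails to converge, and that the report will say which was fitted.

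The cost is one sentence and four more covariance parameters (six instead of two), with a small risk of non-convergence. With three fixed visits and 160 patients, both are negligible. Settling this before outcome data are seen by arm also avoids choosing the covariance from the results.

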### Interim analyses

We do not anticipate significant safety issues associated with the study intervention or participation in the study. However, interim reports of enrollment, outcome completion and safety data will be prepared for the Data and Safety Monitoring Board (DSMB) on a pre-determined schedule. No formal interim analyses for efficacy or futility are planned unless requested by the DSMB.

### Additional analyses

We do not have any additional analyses planned.

### Protocol non-adherence and missing data

We expect missing values to be minimal due to the ability to retrieve the outcome data even for patients who pass away or withdraw from the study through chart review and caregiver-provided information. Missing data on the baseline covariates are expected to be within 5%. Mixed-effects models can account for missing data under the assumption of missing at random (MAR), where it is assumed that missing scores depend on patient covariates in the model as well as the scores at previous time points. In addition, depending on the proportion of losses to follow-up, we will employ a different strategy for sensitivity analyses. If we observe > 5% missing data at the patient-level and an assumption of MAR is plausible, we will perform multiple imputation to address partial data. Missing outcome data will be imputed, and the treatment effect will be estimated under different scenarios to enable comparison of different sensitivity analyses.

### Plans to give access to the full protocol, participant-level data and statistical code

We plan to make the full protocol, deidentified participant-level data, and the statistical code available from the corresponding author on reasonable request.

### Oversight and monitoring

The coordinating center for this trial is Johns Hopkins University, School of Medicine, Department of Surgery, and Division of Surgical Oncology. The trial steering committee meets weekly and is comprised of the lead principal investigator, program manager, research coordinator, and lead CHW, as well as a senior research program coordinator and the clinical research program administrator within the Department of Surgery at Johns Hopkins University.

### Data safety monitoring board

The DSMB is comprised of three independent health services researchers, a community health worker with related expertise, and an unblinded statistician who is not involved in study design or conduct. The DSMB will function independently from the research team throughout the trial to ensure that all study procedures are being performed in accordance with the study protocol. Meetings will be arranged via video conferencing to review protocols, procedures, and concerns related to research integrity. A charter has been established by DSMB members to guide its governance.

### Adverse event reporting and harms

This study does not involve any invasive procedures and as such, there are minimal safety concerns for study participants. Participants will be provided with the lead principal investigator’s contact information and will be advised report any adverse events or potential harms directly to the principal investigator.

### Frequency and plans for auditing trial conduct

Each enrollment site will perform internal quality control of study conduct, data collection, documentation, and completion.

Quality control at the central study site will include the following procedures: (1) the research coordinator will review documentation of the consenting process and completion of the consent documents; (2) the program manager and lead principal investigator will assess data quality on a monthly basis by conducting a random case review of 5% of all clinical data collected that month to assess for missing or incomplete data and excessive variability; (3) the study team will monitor consistent delivery of the study intervention at each enrollment site throughout the trial through monthly meetings and feedback from the lead CHW; (4) the study team will review protocol deviations on an ongoing basis and will implement corrective actions when the quantity or nature of deviations are deemed to be at a level of concern.

### Plans for communicating important protocol amendments to relevant parties

Any significant modifications to the study protocol that could impact study conduct, potential benefits or harms to patients and their caregivers, or participant safety will require a formal protocol amendment. Protocol amendments will be agreed upon by investigators from all enrollment sites and approved by the institutional review board (IRB) at Johns Hopkins University prior to implementation.

### Dissemination plans

The study findings will be presented to the CABs at each enrollment site. We will consider hosting a symposium for all stakeholders, including patients, caregivers, clinicians and other frontline clinical workers, health system leaders, community organizations, advocacy organizations, as well as payors and policymakers. The study findings will also be presented at national and international conferences and a manuscript outlining the study findings will be submitted to a high-impact journal for publication.

## Discussion

The DeCIDE PC intervention utilizes CHWs as palliative care team members with the goal of enhancing palliative care outcomes and reducing disparities for African American patients with advanced cancer. Upon completion of the clinical trial, we will evaluate the implementation of the DeCIDE PC intervention to identify facilitators and barriers to implementation. This will be performed through multilevel analysis of intervention delivery and qualitative interviews with key stakeholders who were involved in implementation of the intervention. We believe this will add insight and context to the summative findings from the effectiveness trial and will contribute to future dissemination efforts.

We expect the DeCIDE PC intervention to improve integration of palliative care, reduce barriers to care, enhance linkage to resources, and improve palliative care outcomes for African American patients with advanced cancer. If found effective, DeCIDE PC may be a transformative model with the potential to guide large-scale adoption of promising strategies to improve palliative care use and will serve as a model for similar action in other academic and community oncology centers.

## Data Availability

The full protocol will be available from the corresponding author on reasonable request. This manuscript does not contain participant-level data.

## Abbreviations

QOL: Quality of life
ASCO: American Society of Clinical Oncology
SDOH: Social determinants of health
CHW: Community health worker
CHWs: Community health workers
DeCIDE PC: Community Health Worker Intervention for Disparities in Palliative Care
ACP: Advance care planning
CAB: Community Advisory Board
CFIR: Consolidated Framework for Implementation Research
RE-AIM: Reach, Effectiveness, Adoption, Implementation, Maintenance
SPIRIT: Standard Protocol Items: Recommendations for Interventional Trials
AJCC: American Joint Committee on Cancer
EMR: Electronic medical record
CAPC: Center to Advance Palliative Care
LW: Living will
DPOA: Durable power of attorney
FACIT-Pal: Functional Assessment of Chronic Illness Therapy - Palliative Care
QOC: Quality of Communication
ESAS: Edmonton Symptom Assessment Scale
CES-D: Center for Epidemiologic Studies Depression Scale
SMD: Standardized mean difference
REDCap: Research Electronic Data Capture
MAR: Missing at random
DSMB: Data and Safety Monitoring Board
IRB: Institutional review board
